#### Analysis population

The primary and secondary endpoints will be analysed on the intention-to-treat (ITT) set consisting of all patients randomized in the study independent of the intervention they receive (analysis ‘as randomized’). The safety analysis will be performed on the safety set consisting of all patients randomized into the study and assigned to the treatment group of their actual treatment.

#### Analysis of the primary endpoint measure

Wound irrigation with PHX solution will be tested for superiority over no irrigation (test 1) and irrigation with saline (test 2) with respect to the incidence of SSI within 30 days postoperatively using two Fisher exact tests with the following hypotheses:

Test 1: *H*
_1_0_ : *π*
_*P*_ = *π*
_*N*_ versus *H*
_1_*A*_ : *π*
_*P*_ ≠ *π*
_*N*_

Test 2: *H*
_2_0_ : *π*
_*P*_ = *π*
_*S*_ versus *H*
_2_*A*_ : *π*
_*P*_ ≠ *π*
_*S*_

where *π*
_*P*_, *π*
_*N*_, and *π*
_*S*_ denote the incidence of SSI in the PHX, no irrigation, and saline groups, respectively. The tests will be performed as two-sided and with a global significance level of 5%. Using the Bonferroni-Holm adjustment, the local significance level will be 2.5% for test 1 and 5% for test 2.

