**Methods/design:**

The IOWISI trial is a multicentre, randomized, observer- and patient-blinded clinical trial with three parallel treatment groups, comparing IOWI with a 0.04% PHX solution to no irrigation (test 1) or saline (test 2) before skin closure after laparotomy for visceral surgery (contamination level II–IV). The primary endpoint of the trial is the SSI rate within 30 days postoperatively. Statistical analysis of the primary endpoint measure will be based on the intention-to-treat population. The global level of significance is set at 2.5% for test 1 and 5% for test 2 and the sample size (*n* = 540) is determined to assure a power of 94% (test 1) and 85% (test 2).

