#### Sample size calculation

The sample size was calculated (nQuery Advisor software version 7.0, Statistical Solutions Ltd, Cork, Ireland) based on the primary endpoints of the study, assuming SSI rates of 2.2% in the PHX group (according to the trial by Roth et al. [17]), 8.7% in the saline group (according to the results of the trial by Cervantes-Sanchez et al. [15]) and 16.2% in the control group (according to results of the meta-analysis by Mueller et al. [14]). The global significance level was set to 5%. Since the PHX arm will be used twice for a comparison, the Bonferroni-Holm procedure was used to set the local alpha level to 2.5% for test 1 (PHX versus no irrigation) and to 5% for test 2 (PHX versus saline). If 230 patients are recruited in the PHX arm, 230 patients in the saline arm, and 80 patients in the control arm (a total of 540 patients), the two-sided Fisher exact test will have a power of 94% for test 1 and 85% for test 2 to detect differences between the treatment groups. The comparison of saline irrigation versus control is not included in the sample size calculation as it will not be analysed in a confirmatory manner; the low medical interest cannot justify the large increase in patient numbers.

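### The plan names Bonferroni-Holm but ties 2.5% to test 1 and 5% to test 2 by label; taken literally this is not Holm and does not guarantee the 5% global level

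*Protocol article*

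**What the plan says.** The trial has two confirmatory tests: PHX against no irrigation (test 1) and PHX against saline (test 2), each a two-sided Fisher exact test.

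- **Analysis of the primary endpoint measure** sets the overall level, "The tests will be performed as two-sided and with a global significance level of 5" (per cent), and then the local levels: "Using the Bonferroni-Holm adjustment, the local significance level will be 2.5% for test 1 and 5% for test 2".
- **Sample size calculation** also gives 5% as the global level. It explains that the PHX arm is used twice and that "the Bonferroni-Holm procedure was used to set the local alpha level to 2.5% for test 1 (PHX versus no irrigation) and to 5% for test", the last figure being for the saline comparison. The powers given are 94% for test 1 and 85% for test 2, with 230, 230 and 80 patients.
- **Abstract, Methods/design** labels the levels differently: "The global level of significance is set at 2.5% for test 1 and 5% for test 2".

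Nowhere does the article say that the p-values are ordered, or that test 2 depends on the result of test 1.

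**The concern.** Holm is a step-down procedure. With two tests its step levels are indeed 2.5% and 5%, but which test receives which level is settled by the data. The 5% step is open only after a rejection at 2.5%, and that condition is what keeps the family-wise error at 5%. If the levels are attached to the tests in advance and both tests are always carried out, the condition is gone and the 5% guarantee goes with it.

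This rule decides both confirmatory claims. An analyst who follows the stated levels and one who follows the named method can reach different conclusions from the same data. If the conflict is noticed only after unblinding, choosing between them could look data-driven.

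**Working it through.** **Inputs.** From the sample size section: arm sizes 230 (PHX), 230 (saline) and 80 (no irrigation); "assuming SSI rates of 2.2% in the PHX group", "8.7% in the saline group" and "16.2% in the control group"; levels 2.5% and 5%; stated power 94% and 85%. From the Background: reported infection rates of 14.5% to 25.0%. The article does not say which two-sided Fisher p-value is meant, so both common versions are shown.

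**1. The plan's own power.** Fisher p-values were enumerated over all binomial outcomes at the design rates. Test 1 at 2.5% has power 94.9% (doubled-tail) or 96.5% (probability-ordered). Test 2 at 5% has 85.4% in both versions. The stated 94% and 85% are reproduced to within 1 point by the doubled-tail version and within 2.5 points by the other.

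**2. Where the two rules part.** Let p1 and p2 be the p-values of tests 1 and 2.

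- Region A: p1 > 2.5% and 2.5% < p2 ≤ 5%. The written rule claims test 2; Holm claims nothing. Example: p1 = 0.40, p2 = 0.04.
- Region B: 2.5% < p1 ≤ 5% and p2 ≤ 2.5%. The written rule fails test 1; Holm rejects both. Example: p1 = 0.04, p2 = 0.01.

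**3. Family-wise error with equal rates in all arms.** Given x infections in the PHX arm, the two tests are independent. Let a(x) be the conditional probability that p1 ≤ 2.5%, and b₅(x) and b₂.₅(x) the conditional probabilities that p2 is at most 5% and 2.5%. Let w(x) be the binomial probability of x. Then

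- written rule: 1 − Σ w(x)·[1 − a(x)]·[1 − b₅(x)]
- Holm: 1 − Σ w(x)·[1 − a(x)]·[1 − b₂.₅(x)]

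| Common SSI rate | Written, probability-ordered | Holm, probability-ordered | Written, doubled-tail | Holm, doubled-tail |
|---|---|---|---|---|
| 5% | 4.64% | 3.16% | 3.90% | 2.39% |
| 8.7% | 5.09% | 3.38% | 4.63% | 2.90% |
| 14.5% | 5.37% | 3.58% | 4.94% | 3.12% |
| 16.2% | 5.50% | 3.65% | 5.09% | 3.21% |
| 20% | 5.62% | 3.73% | 5.27% | 3.38% |
| 25% | 5.72% | 3.82% | 5.45% | 3.54% |

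The written rule is above 5% at 8.7% and the higher rates shown with probability-ordered p-values, and from about 16% with doubled-tail p-values.

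**4. Only one null true.** A false claim can then come from one test only, and that test is run at 2.5% or 5%. The error stays at or below 5%, so the excess is confined to the case where both nulls hold.

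**5. Disagreement and power at the design rates (2.2%, 8.7%, 16.2%).** With probability-ordered p-values, region A has probability 0.39% and region B 0.96%, together about 1.4%. With doubled-tail p-values they are 0.55% and 1.17%, together about 1.7%.

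| | Test 1 | Test 2 |
|---|---|---|
| Written rule, probability-ordered | 96.5% | 85.4% |
| Holm, probability-ordered | 97.4% | 85.0% |
| Written rule, doubled-tail | 94.9% | 85.4% |
| Holm, doubled-tail | 96.1% | 84.8% |

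**The case against.** The strongest defence is that the article names a fully defined procedure and a 5% global level, and that 2.5% and 5% are exactly Holm's two step levels. Test 1 has the larger assumed difference (2.2% against 16.2%, compared with 2.2% against 8.7%), so the labels may simply record the expected order. Some order must be assumed to compute power. This is a fair account of the sample size section, and Holm is quite possibly what was intended. It does not rescue the analysis section, which states the levels by test as the rule to be applied. Nor is this a detail left to a later plan: the article fixes the levels in three places.

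A reader might infer more than the documents support:

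- **That the trial runs at 7.5% error.** The sum 2.5% + 5% = 7.5% is only a bound. A normal approximation, with shared-arm correlation √[(80/310)·(230/460)] = 0.359, gives 7.2%. The planned Fisher tests are conservative and reach neither figure at the rates examined.
- **That the stated power is wrong.** Under Holm, the named procedure, test 2 has about 85%, and 94% for test 1 is on the cautious side. Test 2 falls to about 83% (82% doubled-tail) only if it is run solely after a significant test 1, and the article states no such condition.
- **That a fixed sequence should replace Holm.** That is a design preference. Choosing Holm is legitimate; the error lies in how it is written down.

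The abstract's use of the word global for the local levels is a wording slip, since both statistical sections give 5%.

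**Conclusion.** The rule is wrong as written: the named procedure and the stated levels conflict, and the literal rule does not guarantee the 5% global level that the article claims. The numerical excess is small. At common infection rates of 5% to 25% the error is 4.6% to 5.7% or 3.9% to 5.5%, depending on the Fisher version, against at most 3.8% for Holm. Not guaranteed is therefore the right description, rather than always inflated. The more practical harm is an ambiguous decision rule for both confirmatory claims, although under the optimistic design rates it would change a conclusion in fewer than 2 trials in 100.

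These figures assume complete data on 230/230/80 patients and the literal reading of the analysis section. If the sponsor confirms that Holm was meant, the inference is sound and only the text needs correction. The sample size is not in question.

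**What to change.** In the analysis section, and consistently in the sample size section, state that the smaller of the two p-values is compared with 2.5% and, only if that hypothesis is rejected, the larger is compared with 5%. Delete the assignment of 2.5% to test 1 and 5% to test 2. If the 94% and 85% are kept, describe them as powers of the single tests at planning levels of 2.5% and 5%, or replace them with the Holm values of about 97% and 85%. In the abstract, give the global level as 5%.

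The cost is wording only, with no additional patients and no unfavourable change in power. The change should be documented before unblinding, so that the choice of rule cannot appear to depend on the results.

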#### Sensitivity of the primary endpoint measure

A dropout rate of 8–10% is expected in this study based on experience from similar trials previously conducted in the CHIR-*Net* [1]. The primary endpoint analysis will be based on all patients with complete SSI follow-up. In order to examine the sensitivity of the results, multiple imputations will additionally be used to estimate missing primary endpoint data.

#### Supportive analysis of the primary endpoint

Randomization will be stratified by study centre and level of contamination. Supportive analysis of the primary endpoint will be performed using a binary logistic regression model with dependent variable SSI and the covariates treatment group, study centre, and level of contamination. In addition, the following parameters might influence the outcome which is why they will be included as model covariates:Operation-related risk factors: (a) type of surgery; (b) duration of surgery; (c) use of wound-edge protectors; (d) intraoperative changing of gloves before skin closure; (e) presence of an enterostomy; (f) administration and timing of antibiotic prophylaxis; (g) NNIS risk score;Patient-related risk factors: (h) BMI; (i) ASA score; (j) age; (k) diabetes; (l) duration of preoperative hospital stay; (m) smoking; (n) alcohol abuse; (o) history of SSI; (p) history of radio- and/or chemotherapy.

Furthermore, surgical and patient characteristics will be monitored to identify other potential confounders and to allow adjustment for these variables.

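### The supportive logistic model is committed to at least 29 parameters (centre as fixed effects) on about 38 expected SSIs; fitted by ordinary maximum likelihood it would exaggerate the adjusted odds ratios

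*Protocol article*

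**What the plan says.** Under Supportive analysis of the primary endpoint, the protocol article specifies a binary logistic regression of SSI on treatment group, study centre and contamination level. It goes on: "In addition, the following parameters might influence the outcome which is why they will be included as model covariates". Sixteen items follow, lettered (a) to (p): seven operation-related and nine patient-related. The wording is a commitment, not a list of candidates. The section closes by providing for the monitoring of surgical and patient characteristics "to identify other potential confounders and to allow adjustment for these variables".

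The planning figures are under Sample size calculation: "assuming SSI rates of 2.2% in the PHX group", "8.7% in the saline group" and "16.2% in the control group". The arm sizes are fixed there too: "If 230 patients are recruited in the PHX arm, 230 patients in the saline arm, and 80 patients in the control arm". Trial sites gives at least 10 departments, and Randomization and blinding gives three contamination classes (II to IV). Sensitivity of the primary endpoint measure expects 8–10% dropout.

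**The concern.** A logistic model with about as many coefficients as events is poorly determined. Under ordinary maximum likelihood two things follow. Coefficients are biased away from zero, so the adjusted odds ratios overstate the difference between PHX and the comparators. Some coefficients may also have no finite estimate, because a centre or covariate level contains no SSI.

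This model is the only stated analysis of the primary endpoint that takes account of the stratification factors, and it is there to support the main result. An estimate that leans towards a larger PHX benefit is a poor support.

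Two smaller points belong here. The closing sentence of the section leaves the covariate set open. And two listed items, glove change before skin closure and duration of surgery, may be completed after randomization, which takes place once the fascia is closed and is followed by telling the surgical team the allocation.

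**Working it through.** **The plan's own figure.** The sample size section says that "the two-sided Fisher exact test will have a power of 94% for test 1 and 85% for test 2". Enumerating both binomials, with the two-sided Fisher p-value taken as twice the one-sided value, gives 94.9% and 85.4%. The rates and arm sizes are therefore read as the plan intends.

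**Expected SSIs (n × rate).**
- PHX: 230 × 0.022 = 5.06
- Saline: 230 × 0.087 = 20.01
- No irrigation: 80 × 0.162 = 12.96
- Total: 38.0
- After 8–10% dropout: 38.0 × 0.92 = 35.0 to 38.0 × 0.90 = 34.2

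**Parameters, without the intercept.**
- Treatment, three arms: 2
- Contamination, three classes: 2
- Centre, at least 10 as fixed effects: at least 9
- Items (a) to (p), one each: 16
- Total: at least 29

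This is a floor. Type of surgery, ASA score, NNIS score, and antibiotic administration with timing may each need more than one parameter. With a random centre intercept the count is 2 + 2 + 16 = 20 plus a variance term.

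**Events per parameter.**
- Planning rates: 38.0 / 29 = 1.3; after dropout 34.2 / 29 = 1.2
- Random centre: 38.0 / 20 = 1.9
- Overall SSI rates of 14.5% to 25% (the range in the Rationale): 540 × 0.145 = 78 to 540 × 0.25 = 135 events, or 2.7 to 4.7 per parameter with 29 parameters

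**Simulation.** There were 12 scenarios of 1,000 trials each at the planning rates. Separation was detected by linear programming. Odds ratios come from maximum likelihood fits in the trials without separation. They are compared with the true conditional odds ratio, so the excess is not non-collapsibility. The article does not give the following, so they were assumed: binary covariate prevalences (6% to 93%, or all 50%), covariate effects (none, or log odds ratios of 0.2–0.4, up to 0.8 for class IV), and centre sizes (equal, or proportional to 1/k). Dropout was 0 or 9%.

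| Model | Separation, equal centres | Separation, very unequal centres | Median OR ÷ true conditional OR |
|---|---|---|---|
| 29 parameters | 20–48% | 71–84% | saline 1.12–1.24; no irrigation 1.16–1.39 |
| 13 parameters (treatment, centre, contamination) | 20–28% | 71–78% | 0.96–1.07 |
| 4 parameters (treatment, contamination) | 1–4% | 1–4% | 0.92–1.03 in the scenarios printed |

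A separate simulation with covariates of no effect agrees. The planning odds ratios versus PHX are (0.087/0.913)/(0.022/0.978) = 4.24 and (0.162/0.838)/(0.022/0.978) = 8.59. The 29-parameter maximum likelihood medians were about 4.9 and 10.6, ratios of 1.16 and 1.23. A shorter model with a Firth penalty gave 4.1–4.2 and 8.3–8.4.

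**Can the treatment term itself separate?** The chance of no SSI in the PHX arm is 0.978^230 = 0.6%, or 0.978^209 = 1.0% after 9% dropout.

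**The case against.** The article names no estimator and does not say whether centre is fixed or random. Those choices, and a rule for non-convergence, can properly sit in an analysis plan that is not shown, so their absence is not criticised here. This stands: the 29 depends on fixed centre effects, and the bias and separation figures depend on ordinary maximum likelihood. The list (a) to (p) does not depend on either, and 20 parameters on 38 events is still too many.

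A reader might infer that the covariate list causes the separation. The simulations do not support that. With very unequal centres the 13-parameter model separates almost as often as the full one, and the 16 items add noticeably only when centres are equal and some covariates are rare. A reader might also infer that the treatment effect would be inestimable. Most separation falls in centre and rare-covariate terms, and an empty PHX arm is a 1% event at most.

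Nor should the closing sentence be read as a licence for selective adjustment. The statistician is to be blinded to allocation, and the text speaks of monitoring rather than a search. That protection is partial, since an arm of 80 against two of 230 reveals the control group. The glove and duration points are possible but unquantified: Data collection and management records glove changes during the operation generally, and only the irrigation and skin-closure part of the duration follows randomization.

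Finally, the analysis is labelled supportive. Neither the Fisher tests nor the multiple-imputation analysis needs it.

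**Conclusion.** The point holds for the supportive model only. The article commits it to at least 29 parameters with fixed centres (about 20 plus a variance term if random) on about 38 expected SSIs, or 34–35 after dropout. Fitted by ordinary maximum likelihood, it would typically exaggerate the odds ratios versus PHX by roughly 10–25% for saline and 15–40% for no irrigation. Some centre or rare-covariate terms would be non-estimable in roughly 20–50% of trials with equal centres and 70–85% with very unequal centres.

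The counts follow from the document. The bias and separation ranges rest on assumed prevalences, effects and centre sizes, so no single percentage should be quoted. The bias is also measured only in trials without separation, which are a minority when centres are very unequal. Higher SSI rates would ease the problem without removing it.

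It would be wrong to conclude that the trial's main result is at risk: the confirmatory tests are untouched. This is a cheap improvement.

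**What to change.** - Limit the supportive model to treatment, contamination level and centre, with centre as a random intercept or with small centres pooled, plus a short list of covariates named in advance and fixed before randomization.
- Fit it with Firth penalised likelihood. Shortening the list removes most of the exaggeration, but separation from small centres remains unless centre is handled and the likelihood penalised.
- Describe the other risk factors by arm.
- Let the pre-named list replace the open provision for other confounders.
- Use glove change and duration of surgery as covariates only if they are recorded up to fascial closure, before randomization.

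The cost is a few lines of text before analysis. The small downside is that fewer factors are adjusted for at once.

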#### Analysis of secondary endpoint measures

Secondary endpoints will be analysed by treatment arm on the ITT set using appropriate descriptive statistics. Any explorative statistical testing will be performed using a significance level of 5%.

#### Safety analysis

All AE/SAEs will be analysed with incidence rates by treatment group and according to severity. All AE/SAEs rated as related to the study treatment will be listed separately. For the comparisons between groups, the Chi-square test and the Fisher exact test will be used if appropriate.

### Withdrawals

Patients are free to withdraw from trial participation at their own request at any time and without giving reasons for their decisions. Withdrawals will be documented in the eCRF and in the patient’s medical record. However, all on-going SAEs must be followed up and documented until their final outcome can be determined. In addition, the investigator has the right to withdraw a patient from the study at any time. Reasons for withdrawal from the study may include but are not limited to the following: (a) any medical condition that the investigator or sponsor determines may jeopardize the patient’s safety if he or she continues in the study; (b) if it is discovered that a study subject is pregnant or may have been pregnant at the time of intervention. Patients who withdraw from the study will not be replaced.

### Stopping guidelines

The trial can be prematurely closed by the sponsor in consultation with the responsible biostatistician for the following reasons: (a) it appears that patient enrolment is unsatisfactory with respect to quality or quantity, or data recording is severely inaccurate or incomplete; (b) there is external evidence demanding a termination of the trial, e.g. indicating that the rate or severity of SAEs or morbidity in this trial poses a potential health hazard caused by the intervention in one of the trial groups. In case of premature closure, the ethics committee and federal authority must be informed.

### Registration

The trial protocol was registered at the German Clinical Trials Register (part of the WHO International Clinical Trials Registry Platform) under the trial number DRKS00012251 on 3 July 2017.

### Good clinical practice

The procedures set out in this trial protocol, pertaining to the conduct, evaluation, and documentation of this trial, are designed to ensure that all persons involved in the trial abide by GCP [21] and the ethical principles described in the current version of the Declaration of Helsinki [23]. The trial will be carried out in keeping with all federal and local legal and regulatory requirements.

## Discussion

Currently, the official recommendations on the prophylactic use of IOWI and clinical practice vary largely. The WHO Global Guidelines for the prevention of SSI (2016) as well as the updated CDC guidelines (2017) conclude that there is insufficient evidence to recommend IOWI with saline and that IOWI with diluted PVP-I could be considered but also not routinely recommended [9]. However, the level of underlying evidence is low and trials analysed for these guidelines do not solely focus on visceral surgery, but include all types of surgery (e.g. orthopaedic or neurosurgery) which differ substantially in SSI rates and causative microorganisms. Furthermore, PVP-I solutions are seen as controversial for this prophylactic indication due to possible systemic adverse effects and tissue toxicity. However, despite its unproven efficacy, most general and visceral surgeons currently use IOWI to prevent SSI [25].

Solutions containing the antiseptic agent PHX are approved for IOWI, and were shown to be tissue tolerable and effective in vitro and in vivo [8, 9]. However, PHX solutions are not mentioned in the WHO or other recent guidelines. Ultimately, data from high-quality RCTs are needed to resolve the scientific equipoise regarding application of IOWI with saline or antiseptics.

The IOWISI trial has a pragmatic, three-armed study design (PHX *versus* saline irrigation *versus* no irrigation) and shall be conducted in at least 10 centres within the German Surgical Trial Network (CHIR-*Net*). A multicentre approach, including hospitals of different care levels, was chosen to increase external validity. Internal validity and data quality assurance are established by adherence to the SPIRIT statement and GCP regulations regarding recruitment, training of study personnel, methods against bias, outcome reporting, and documentation.

All patients undergoing visceral surgery by laparotomy within 27 months will be screened for this trial. Broad inclusion criteria were applied to ensure rapid and sufficient recruitment of the target sample size.

After closure of the abdominal fascia according to local standards, laparotomy wounds will either be irrigated with PHX or saline. The volume of 1000 ml was chosen to be sure that large laparotomy wounds would be sufficiently irrigated. This was determined by the clinical experience of senior surgeons at our institution since, so far, no recommendations for the optimal volume of surgical wound irrigation exist. The same applies to the duration and technique of irrigation. However, the POLIS pilot trial compared “short” versus “long” irrigation with PHX and no differences in SSI rates were observed [18]. In vitro experiments show that a contact time of 10–15 min is required for PHX to act fully [12]. To ensure this, the irrigation technique will be standardized in the IOWISI trial. In addition, wounds will be left moistened with the PHX solution at the end of the irrigation and shall not be rubbed dry with abdominal cloths or rinsed with saline again.

The primary endpoint is the incidence of SSI 30 days postoperatively, according to the widely accepted CDC definition and classification (Table 1) [19]. Since many different SSI definitions have been proposed over the past decades, standardized reporting is crucial for the comparability of trials regarding SSI prevention.

The results of this pragmatic trial will provide high-level evidence for clinical recommendations regarding the use of IOWI with PHX or saline to prevent SSI after laparotomy, potentially impact future clinical guidelines and provide participating patients the opportunity of an improved treatment.

